### **8.3. Clinical monitoring of participants**

During this period, clinical (1x/day) and laboratory (1x/day) examinations will be performed daily. Considering the national recommendation, this study will classify the patient according to the local aspects of the lesion for laser application:

| Local Aspects | Edema    | Pain
(numerical
scale) | Temperature
(contralateral
difference) |
|----------------------|-----------------|---------------------------------------|-------------------------------------------------------|
| Light                | 1 to 2 segments | 0-3                                   | Up to 0.5 °C                                          |
| Moderate             | 3 to 4 segments | 4-7                                   | 0.6-1 °C                                              |
| Severe               | 5 segments      | 7-10                                  | More than 1 °C                                        |

\* ADAPTED (38).

c. Participants in arms 1 and 2 will receive clinical evaluation and classification and tests related to inflammation and myonecrosis will be performed during the 3 days of hospitalization.

d. For the evaluation, a clinical form will be used with data on local and systemic signs and symptoms, daily evolution of the patient, evaluation of the wound site at all verification times, demographic data and laboratory tests, and laser application. (see Appendix A).

### **e. 8.4. Device storage conditions**

#### **8.4.1 Environmental operating conditions**

- Room temperature +15 °C to +30 °C
- Relative humidity 30% to 75% (non-condensing)
- Atmospheric pressure 700 hPa to 1,060 hPa

[figure not shown][figure not shown]

---

#### 8.4.2 Environmental transport and storage conditions

- Room temperature -12 °C to +50 °C
- Relative humidity 0% to 90% (non-condensing)
- Atmospheric pressure 700 hPa to 1,060 hPa

#### 8.4.3 Device cleaning

- For cleaning, bactericidal substances, such as 70% alcohol or surface disinfectant, can use be used. Do not let liquid penetrate inside the case or battery charger;
- Glasses can be cleaned by washing with water and neutral soap, drying lightly with paper tissues;
- The nozzle of the laser pen has a micro lens and a glass window at the beam output. This nozzle has metal and glass parts; therefore, it can be autoclaved and, periodically, the external parts of the window and micro lens must be cleaned with cotton or tissue paper (slightly moistened with alcohol) to remove residues that alter the output power of the beam.
- The pen body cannot be immersed in liquids (water, alcohol, solvent, etc.);
- The pen cannot be placed in ovens or autoclaves. Only the nozzle can be placed in autoclaves;
- Keep the battery contact terminals clean at all times. Use only a clean, dry cloth to clean the terminals.

#### 8.4.4 Battery

- Do not expose the battery to high temperatures (above +45 °C in operation or load) or fire due to risk of explosion;
- Always keep the battery charged, always leave the battery charging when not in use;

[figure not shown][figure not shown]

- 
- Charge the battery in an environment that is at room temperature;
  - Use only the charger that comes with the equipment;
  - Do not use the flexible battery charger power cable if parts of it are squashed or if the insulation is damaged;
  - Do not short-circuit the battery terminals;
  - Do not allow metallic objects to make contact with the battery terminals;
  - If the equipment remains stored for a long period, recharge the battery every 6 months;
  - The battery must only be replaced by authorized technicians.

**f. 8.5 Responsibilities**

The investigator or other staff member permitted to store the laser is responsible for ensuring that the product used in the clinical trial is maintained safely as specified by the manufacturer and in compliance with applicable regulatory requirements.

All products must be distributed according to the study arm, by a previously designated researcher to ensure that an accurate record is maintained. A record of all study evaluations will be maintained in the investigator's file at the site (ISF) for the study. Data regarding the date of receipt, energy level, number of points, applications and date of use will be recorded for each laser application. A laser logbook will be maintained at the study clinic.

[figure not shown][figure not shown]

## 9. EVALUATION OF OUTCOMES

### 9.1. Primary

- g. Decreased inflammation.

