## 5. STUDY OBJECTIVES

### 5.1 Primary

To evaluate the effectiveness of low-power laser in the recovery of acute local manifestations in victims of *Bothrops* envenomations.

Clinical and biological tolerability:

- Clinical tolerability: No appearance of myonecrosis.
- Biological safety: CK (creatine kinase).

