### 5.2. Secondary

Evaluate the sociodemographic aspects of victims of *Bothrops* envenomations;

Describe the clinical aspects of victims of *Bothrops* envenomations with alterations in the site of the bite;

Compare different laser application protocols at sites of envenomation with inflammatory manifestations;

Evaluate the safety of the laser protocol in regards to the local effects of snakebites.

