#### b. 6.2 Study duration

All patients presenting with FMT-HVD bitten by a *Bothrops* snake will be submitted to the standard evaluation. Selected participants will be randomized to one of three treatment regimens at the time. The treatment period will last for 3 days, with 3 days of laser application. The study will run from January 2019 to July 2021.

After the follow-up of the study, the patient will be instructed to seek the study center at any time if they have a complaint related to the snakebite.

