### 9.1.3 Assessment methods

Physical and clinical signs and symptoms: the following local signs and symptoms will be systematically examined by the investigator and described as being absent or present, with grading of intensity depending on the sign/symptom: pain, redness, edema and heat (temperature).

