## 9.2 Secondary

### Prevention of myonecrosis

Efficacy should be evaluated according to the results of creatine kinase (CK) in the follow-up period (see Appendix A).

- The increase in CK indicates myonecrosis, which should be investigated from the first moment with the patient and after 24 h, 48 h and 72 h. When the patient returns on the 7th day, CK testing will also be performed and evaluated in the two arms of the clinical trial.

Other secondary parameters include:

- Proportion of any adverse events, such as itching, skin redness, changes in skin pigmentation, bruising, scarring, peeling, skin depression, and textural and thickness changes.

[figure not shown][figure not shown]

---

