### 13.2 Statistical and analytical plans

Feasibility outcomes were analyzed using descriptive statistics as proportions. Trial outcomes were reported as means and standard deviations. We report the outcomes using means and standard deviations, and we conducted inferential analysis on our data in order to report the differences between the two groups. Mean values of creatine phosphokinase activity, pain intensity, circumference measurement ratio, extent of edema, difference between the bite-site temperature and that of the contralateral limb, and disability assessments, were compared using the t-test for independent samples, at 48 hours after admission. A Kaplan-Meier survival analysis with a log-rank test was performed to detect differences in the time elapsed from admission to the day of reduction by 50% in creatine phosphokinase activity, pain intensity, circumference measurement ratio, extent of edema and difference between the bite-site temperature and that of the contralateral limb between the intervention and comparator groups, at two points - on 24 and on 48 hours after admission. The comparison of the frequency of use of analgesics, secondary infections and necrosis in a follow-up of 48 hours, between the intervention and comparator groups, was made using the Chi-square or Fisher's exact test; odds ratios with 95% confidence intervals were obtained. The Kruskal-Wallis rank sum test was used to compare the disability scores between groups, for each domain score and for the summary score. Statistical analyses were performed in the R software in the IDE Rstudio environment (version 4.1.2), and the significance level of the tests was 0.05.

[figure not shown][figure not shown]

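### The primary outcome is not tied to one variable, time point and test: section 13.2 runs at least 15 comparisons at 0.05 (8 to 12 on the measured inflammation signs) and designates none as primary

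*Protocol*

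**What the plan says.** Protocol section 5.1 states the primary objective as "To evaluate the effectiveness of low-power laser in the recovery of acute local manifestations in victims of" *Bothrops* envenomations. Under the same heading it adds tolerability items, one of them "Biological safety: CK (creatine kinase").

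Section 9.1 gives the primary outcome as "Decreased inflammation" and nothing more. Section 9.1.3, still under the primary heading, has local signs recorded as absent or present with "grading of intensity depending on the sign/symptom: pain, redness, edema and heat (temperature"). It sets no composite, no leading sign, no time point and no definition of a decrease.

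Section 9.2 (Secondary), under prevention of myonecrosis, says: "Efficacy should be evaluated according to the results of creatine kinase (CK) in the follow-up period".

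Section 13.2, repeated in the Synopsis, starts its list of tests with "Mean values of creatine phosphokinase activity, pain intensity, circumference measurement ratio, extent of edema". It adds temperature difference and disability, all by t-test at 48 hours. Log-rank tests, chi-square or Fisher tests and Kruskal-Wallis tests follow. The level is 0.05 throughout, and no comparison is called primary.

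**The concern.** A trial meets or misses its primary outcome on the result of a designated comparison. Here the outcome is named in words that match no tested variable, and the analysis section offers a list in which several entries could be presented afterwards as the answer. The error rate on the primary question is then not held at 5%.

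The Synopsis also plans an interim analysis that looks at the primary outcome and may lead to continuing, restructuring or ending the study. That decision has no defined quantity to rest on.

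Two mismatches make the link between outcome and analysis weaker still. Redness, one of the four signs in 9.1.3, enters no test in 13.2. CK sits under the primary objective in 5.1 and under the secondary outcome in 9.2, so its tier is unclear.

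**Working it through.** **Step 1. Count the comparisons in section 13.2.**

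- t-tests at 48 hours: CK, pain, circumference ratio, edema extent, temperature difference, disability = 6
- log-rank tests, time to a 50% reduction: the same list without disability = 5 (10 if run at both 24 and 48 hours)
- chi-square or Fisher tests: analgesic use, secondary infection, necrosis = 3
- Kruskal-Wallis tests: disability summary score = 1, plus each domain (number of domains not given)

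Minimum: 6 + 5 + 3 + 1 = 15. With one domain score and both log-rank time points: 6 + 10 + 3 + 2 = 21.

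**Step 2. Count only those that bear on the signs in 9.1.3.** The variables are pain, circumference ratio and edema extent (both for edema), and temperature difference (for heat). That gives 4 t-tests + 4 log-rank tests = 8, or 4 + 8 = 12 with both log-rank time points. Redness contributes none.

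**Step 3. Chance of at least one p<0.05 when the laser has no effect.** The protocol does not state sidedness; two-sided tests are assumed.

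If independent, either direction: 1 − 0.95^k.

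- k = 8: 1 − 0.95^8 = 0.337
- k = 12: 1 − 0.95^12 = 0.460
- k = 15: 1 − 0.95^15 = 0.537

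If independent, only results favouring the laser: 1 − 0.975^k.

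- k = 8: 0.183
- k = 15: 0.316

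The outcomes are in fact correlated, and the protocol gives no correlations. A common correlation ρ was therefore assumed. Test statistics were simulated as √ρ·c + √(1−ρ)·e, with c a standard normal value shared by all tests and e a separate one for each test. There were 200,000 draws and the cut-off was 1.96.

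| Tests | Direction | ρ = 0 | ρ = 0.5 | ρ = 0.9 |
|---|---|---|---|---|
| 8 | either | 34% | 25% | 12% |
| 8 | favours laser | 18% | 13% | 6% |
| 12 | either | 46% | 32% | 13% |
| 12 | favours laser | 26% | 16% | 7% |
| 15 | either | 54% | 36% | 14% |
| 15 | favours laser | 32% | 18% | 7% |

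The benchmark for one test is 5% in either direction and 2.5% in favour of the laser. At ρ = 0.5 the favourable-only figures are 12.5/2.5 = 5 times the benchmark for 8 tests and 18.1/2.5 = about 7 times for 15.

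**Step 4. What one designated test would give.** The total of 60 patients cannot be reproduced, because no effect size, standard deviation or power is stated. As a guide only, 30 per arm at two-sided 0.05 and 80% power detects (1.960 + 0.842) × √(2/30) = 0.72 standard deviations. If all 15 comparisons were kept as equals with a Bonferroni correction, each would be tested at 0.05/15 = 0.0033 and the detectable difference would rise to 0.98. At an assumed true difference of 0.8, power would fall from 87% to about 57%.

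**The case against.** The outcome is not without content. Section 9.1.3 names four signs, section 8.3 gives grading cut-offs for edema, pain and temperature, and 13.2 sets 48 hours for the comparison of means. This stands: the defect is that the signs are neither ranked nor combined, not that nothing is specified.

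A reader might infer that any of the 15 comparisons could be declared the primary result. The documents do not support that in full. Section 9.2 labels CK and prevention of myonecrosis secondary, although 5.1 places both under the primary objective. Analgesic use, infection and disability are not signs in 9.1.3. On a strict reading, 8 to 12 comparisons compete.

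A reader might also take 54% as the chance of a false claim of benefit. It is neither restricted to benefit nor realistic as to independence. The log-rank tests reuse the t-test variables, and circumference ratio and edema extent both measure swelling, so high correlations are plausible.

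CK can serve both as a safety marker and as a measure of myonecrosis without contradiction, and standing first in the list in 13.2 gives it no role. Only its placement in two tiers is at fault.

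Finally, one might conclude that the case report form has no disability instrument. The attachments do not allow this: item numbering passes from section 2 to section 8, so pages are missing from view. What can be said is that section 9 does not list disability.

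A statistical analysis plan may exist and may handle adjustment among secondary tests. It does not excuse a protocol that names a primary outcome and sets out its own tests without connecting the two.

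**Conclusion.** The point holds. As written, no result can be said to meet or fail the primary outcome, and the error on the primary question is uncontrolled.

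The range that best fits the text is the one for 8 tests: 34% down to 12% in either direction, or 18% down to 6% in favour of the laser, as the assumed correlation goes from 0 to 0.9. The wider count of 15 raises this to 54% down to 14%, or 32% down to 7%. Even at ρ = 0.9 the favourable-only chance is more than twice the 2.5% of a single test. These figures rest on two-sided testing, a common correlation and normal test statistics, all assumed here.

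The untested redness and the two tiers for CK are confirmed.

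A separate inconsistency is also confirmed. Section 6.2 says "Selected participants will be randomized to one of three treatment regimens at the time", and section 5.2 sets the objective "Compare different laser application protocols at sites of envenomation with inflammatory manifestations", while sections 6.1 and 7.1 describe two arms with one active regimen. It adds nothing to the multiplicity argument.

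**What to change.** - In 5.1, 9.1 and 13.2, name the same single primary variable, time point and test, at two-sided 0.05. Two options use data already collected: circumference ratio at 48 hours, or one global rank test over pain, circumference ratio, edema extent and temperature difference at 48 hours.
- Fix this before any unblinded look, the interim analysis included. Section 13.2 is written in the past tense, so the sponsor should state whether such a look has already taken place. If it has, the choice must be reported as made afterwards.
- Label all other comparisons secondary or exploratory. A Holm correction among them is optional.
- Put CK in one tier, the same in 5.1 and 9.2.
- List disability as an outcome in section 9, or remove it from 13.2. State how redness is to be used.
- Separately, reconcile 6.2 and the laser-protocol objective in 5.2 with the two-arm design.

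The cost is protocol wording, with no extra patients or measurements. The price is that the other comparisons lose confirmatory status. A single-sign primary also leaves the remaining signs as supporting evidence only, which the global rank test avoids at the expense of a result that is harder to express in clinical units.

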#### 9.1.1 Clinical tolerability

i. Clinical data will be collected from the site of the bite and its evolution in the first 3 days, observing all and any signs. At each visit, the investigator will ask the patient about their symptoms, whether they have had any adverse events since their last visit, in addition to performing a standard physical examination.

#### ii. 9.1.2 Biological tolerability

Assessments of laboratory exams will be performed on admission and laser applications in all groups along with the assessments. The tests requested will be HMG (CBC), CK (creatinase kinase), AST (aspartate aminotransferase), LDH (lactic dehydrogenase), and CT (coagulation time).

Blood samples for hematology and clinical biochemistry will be collected from patients via venipuncture. About 10 ml of blood will be collected from each patient for hematology during these visits.

- Hematological parameters: erythrocytes, hemoglobin, platelets, leukocytes and reticulocytes. These parameters will be obtained from a complete blood count and CT.

[figure not shown][figure not shown]

- 
- Biochemical parameters: blood levels of creatinine, AST, LDH. These parameters will be measured according to the enzymatic assay methods for each parameter.

### 9.1.3 Assessment methods

Physical and clinical signs and symptoms: the following local signs and symptoms will be systematically examined by the investigator and described as being absent or present, with grading of intensity depending on the sign/symptom: pain, redness, edema and heat (temperature).

## 9.2 Secondary

### Prevention of myonecrosis

Efficacy should be evaluated according to the results of creatine kinase (CK) in the follow-up period (see Appendix A).

- The increase in CK indicates myonecrosis, which should be investigated from the first moment with the patient and after 24 h, 48 h and 72 h. When the patient returns on the 7th day, CK testing will also be performed and evaluated in the two arms of the clinical trial.

Other secondary parameters include:

- Proportion of any adverse events, such as itching, skin redness, changes in skin pigmentation, bruising, scarring, peeling, skin depression, and textural and thickness changes.

[figure not shown][figure not shown]

---

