#### **7.4. Criteria for discontinuing treatment**

Treatment can be stopped if there is an increase in CK or inflammatory markers: pain, heat, edema, and redness or in cases of secondary infection.

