#### **7.5. Criteria for study interruption**

If the study does not show benefits, for example, the control group shows improvement and the low-power laser groups do not. The presence of marked myonecrosis will also indicate the need for the discontinuation of the study.

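### Section 9.2 lets a CK rise of no stated size or comparator stand for myonecrosis, which as a yes/no rule would not measure it; the planned 48 h CK test also leaves the admission value unused

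*Protocol*

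**What the plan says.** Section 9.2 names prevention of myonecrosis as the secondary outcome and ties it to CK: "Efficacy should be evaluated according to the results of creatine kinase (CK) in the follow-up period". It then gives the interpretation: "The increase in CK indicates myonecrosis, which should be investigated from the first moment". Sampling is at first contact "and after 24 h, 48 h and 72 h", and again a week later: "When the patient returns on the 7 th day, CK testing will also be performed". No fold change, comparator (admission value, previous value or reference limit) or persistence requirement is given.

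Related terms appear in four other places:

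- Section 5.1 sets a yes/no criterion, "Clinical tolerability: No appearance of myonecrosis", and lists CK on a separate line as biological safety. The synopsis safety criteria make the same split.
- Section 7.4: "Treatment can be stopped if there is an increase in CK or inflammatory markers". Again no size is stated.
- Section 7.5: "The presence of marked myonecrosis will also indicate the need for the discontinuation of the study". The degree is not defined and CK is not mentioned.
- Section 13.2 compares mean CK between arms at 48 h by t-test and time to a 50% CK reduction by log-rank test. Separately, it compares analgesic use, "secondary infections and necrosis in a follow-up of 48 hours" by Chi-square or Fisher's test. Necrosis is not defined there.

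**The concern.** Section 9.2 contains the protocol's only statement of what indicates myonecrosis, and that statement has no size or reference point. Section 5.1 turns the absence of myonecrosis into a tolerability criterion. Whoever has to decide whether that criterion was met may therefore reach for the CK sentence and class a patient as a case on any later value above admission.

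Such a flag would depend on how many samples were taken and on whether CK was drifting up or down, not only on muscle injury. If a CK rise is myonecrosis, the two lines in section 5.1 are one criterion. If it is not, the sentence in section 9.2 is wrong as an outcome rule.

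A second weakness sits beside it. The comparison of CK levels that is planned, the 48 h t-test, makes no use of the admission value, although every patient has one.

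**Working it through.** The protocol gives no CK cut-off, no expected rate of myonecrosis and no power statement behind its 60 patients, so there is no figure to reproduce.

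**Inputs from the protocol**
- Follow-up CK at 24, 48 and 72 h and day 7 (9.2): k = 2 samples by 48 h, k = 4 in all.
- 30 patients per arm (synopsis); significance level 0.05 (13.2), taken here as two-sided.

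**Assumptions, not in the protocol**
- Log CK has SD 1 at each visit and the same correlation ρ between any two visits.
- All follow-up means are shifted from admission by δ SD.
- The laser effect on log CK at 48 h is 0.6 SD.

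**Step 1. How often would any rise above admission occur?**

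With φ and Φ the standard normal density and distribution function,

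P(at least one of k later values exceeds admission) = 1 − ∫ φ(z) · Φ(z − δ/√(1−ρ))^k dz.

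For δ = 0 this reduces to k/(k+1) whatever ρ is, because each of the k+1 values is equally likely to be the largest:
- by 48 h: 2/3 = 67%
- to 72 h: 3/4 = 75%
- with day 7: 4/5 = 80%

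For other courses at ρ = 0.6, √(1−ρ) = 0.632:

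| Shift from admission | By 48 h (k = 2) | Four samples (k = 4) |
|---|---|---|
| fall of 1 SD | about 22% | 32% |
| none | 67% | 80% |
| rise of 0.5 SD | 85% | 93% |

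A second model assumes an exponential decline with within-person variation (CV) of 10% to 30%, and uses four samples:

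| CK course | Flagged at CV 10% / 20% / 30% |
|---|---|
| flat | 80% / 80% / 80% |
| half-life 7 days | 28% / 48% / 57% |
| half-life 4 days | 11% / 32% / 43% |
| half-life 2 days | 0.7% / 11% / 22% |

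Neither model contains a myonecrosis term, yet the flagged share runs from under 1% to over 90%.

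**Step 2. What is lost by ignoring admission CK at 48 h?**

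To isolate the effect of adjustment, both tests are put on the log scale.

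Unadjusted t-test: noncentrality = 0.6 × √(30/2) = 0.6 × 3.873 = 2.32 on 58 degrees of freedom, power 63%.

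Adjusting for log admission CK multiplies the residual SD by √(1−ρ²), so the effect becomes 0.6/√(1−ρ²), on 57 degrees of freedom:

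| ρ | Effect in residual SD | Noncentrality | Power |
|---|---|---|---|
| 0.4 | 0.655 | 2.54 | 70% |
| 0.6 | 0.750 | 2.90 | 81% |
| 0.8 | 1.000 | 3.87 | 97% |

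**The case against.** The strongest reply is that the sentence in section 9.2 only explains why CK is the chosen marker. Nowhere does the protocol say that a patient with any value above admission is a myonecrosis case. The admission comparator and the any-visit logic are a literal reading, not a stated rule. Section 13.2 analyses CK as a mean and as time to halving, and no test counts risers. Necrosis in section 13.2 is not tied to CK, and the clinical form on Attachment B already has a blackened, necrotic category for the bite site. Marked myonecrosis in section 7.5 does not refer to CK. All of this stands, and it limits the point.

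A reader might go further and infer that most patients in both arms would be classed as cases by fluctuation alone, so that the outcome saturates and the trial could show neither prevention nor tolerability. The documents do not support that. The 67% and 80% need a flat course, whereas section 13.2 itself provides for CK falling by half. If CK rises after the bite, the flags reflect real change rather than noise. Even on a flat course, with the laser lowering CK by 0.6 SD at ρ = 0.6, the formula in step 1 gives 80% flagged in control and 52% under laser, which is not saturation. The 80% also needs the day 7 sample, while the necrosis comparison stops at 48 h.

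A reader might also point to the empty CK reference cell on Attachment C. That table is broken in the text available, so nothing here rests on it.

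It can also be said that cut-offs and covariate adjustment belong in a statistical analysis plan. That would answer a silent protocol. This one states an interpretation of CK and names an unadjusted test, so a later plan would have to carry both forward or depart from them.

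**Conclusion.** The point holds in limited form. Section 9.2 equates a CK increase of no stated size or comparator with myonecrosis, in conflict with the separate listing in section 5.1. Applied literally, the flag would not measure myonecrosis: 67% by 48 h and 80% over four samples if CK is stable, about 22% and 32% with a 1 SD fall, and more if CK rises. The stable-course figures need only exchangeable values; the others rest on the assumed shift and correlation. It does not follow that patients will be classed this way, or that the planned CK tests are invalid.

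The free gain is in the 48 h comparison: from about 63% power to between 70% and 97%, depending on a correlation and an effect size that the protocol does not give. The direction of the gain does not depend on the 0.6 SD chosen, provided that admission and 48 h CK are appreciably correlated.

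**What to change.** 1. In section 9.2, remove the sentence equating a CK increase with myonecrosis as an outcome rule. CK can stay as the biochemical measure of muscle injury.
2. In section 13.2 and the matching synopsis text, replace the unadjusted t-test on mean CK with a comparison of log CK at 48 h adjusted for log admission CK, with 24 h as supportive.
3. State that the necrosis count in section 13.2 comes from the bite-site examination on Attachment B, under one definition fixed before unblinding. The page reproduced is for day 1; section 8.3 already calls for wound-site evaluation at every verification time.
4. Reconcile sections 5.1, 7.4, 7.5, 9.2 and 13.2, which use CK increase, myonecrosis, marked myonecrosis and necrosis without saying how they relate. The clinical meaning of each term, and any threshold, is for the investigators; none is proposed here.

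The cost is protocol and analysis-plan wording. No new samples, visits or patients are needed.
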